## Abstract

**Background:**

In 2009, the Steering Committee for Pregnancy and Childbirth in the Netherlands recommended the implementation of continuous care during labor in order to improve perinatal outcomes. However, in current care, routine maternity caregivers are unable to provide this type of care, resulting in an implementation rate of less than 30%. Maternity care assistants (MCAs), who already play a nursing role in low risk births in the second stage of labor and in homecare during the postnatal period, might be able to fill this gap. In this study, we aim to explore the (cost) effectiveness of adding MCAs to routine first- and second-line maternity care, with the idea that these MCAs would offer continuous care to women during labor.

**Methods:**

A randomized controlled trial (RCT) will be performed comparing continuous care (CC) with care-as-usual (CAU). All women intending to have a vaginal birth, who have an understanding of the Dutch language and are > 18 years of age, will be eligible for inclusion. The intervention consists of the provision of continuous care by a trained MCA from the moment the supervising maternity caregiver establishes that labor has started. The primary outcome will be use of epidural analgesia (EA). Our secondary outcomes will be referrals from primary care to secondary care, caesarean delivery, instrumental delivery, adverse outcomes associated with epidural (fever, augmentation of labor, prolonged labor, postpartum hemorrhage, duration of postpartum stay in hospital for mother and/or newborn), women’s satisfaction with the birth experience, cost-effectiveness, and a budget impact analysis. Cost effectiveness will be calculated by QALY per prevented EA based on the utility index from the EQ-5D and the usage of healthcare services. A standardized sensitivity analysis will be carried out to quantify the outcome in addition to a budget impact analysis. In order to show a reduction from 25 to 17% in the primary outcome (alpha 0.05 and bèta 0.20), taking into account an extra 10% sample size for multi-level analysis and an attrition rate of 10%, 2 × 496 women will be needed (*n* = 992).

**Discussion:**

We expect that adding MCAs to the routine maternity care team will result in a decrease in the use of epidural analgesia and subsequent costs *without* a reduction in patient satisfaction. It will therefore be a cost-effective intervention.

**Trial registration:**

Trial Registration: Netherlands Trial Register, NL8065. Registered 3 October 2019 - Retrospectively registered.

## Background

Childbirth is a life-changing event for all women, resulting in various emotions. In modern society, birth often takes place in a clinical environment, which may increase feelings of loss of control and anxiety [1]. Studies show that 20% of women in high-income countries fear childbirth. These women are more likely to request an epidural or even a caesarean section [2]. Anxiety in pregnancy is associated with more interventions during birth. Randomized controlled trials have shown that women who are provided with continuous support during labor and birth need fewer medical interventions, have improved neonatal outcomes, and report a more positive childbirth experience [1]. Women benefit from informational, emotional, physical and practical support during labor [3]. A member of staff, a doula, or a lay-person from the woman’s own network may offer continuous support in the form of improved communication, the provision of coping or massage techniques, assistance with finding the right position, and help with decision-making. This kind of support has been shown to improve both women’s satisfaction with birth experience and childbirth outcomes [1, 3–7]. Subgroup analysis in a Cochrane systematic review suggested that support was most effective when provided by someone in a (trained) doula role [1]. Both the World Health Organization and the Steering Committee for Pregnancy and Childbirth in the Netherlands have recommended the provision of continuous support during labor [1, 8], but the actual implementation of this support remains a challenge. In a pilot study conducted by the Royal Dutch Organization of Midwives, 101 of 125 participating women (80%) indicated that they wanted to receive continuous care during labor, and a reduction in both transfer to secondary care and request for pain medication was observed when this care was provided [9, 10].

In the Netherlands, midwives provide pregnancy, birth and postnatal care to healthy, low-risk women. These women can choose to give birth at home or in a hospital. Based on national guidelines [11], a risk assessment is performed for each pregnant woman during pregnancy and delivery. This risk assessment can result in transfer of care between midwife and obstetrician at any time during pregnancy or delivery. Maternity care assistants (MCAs) assist the midwife during the last part of the first stage and in the second stage of birth. For both low- and high-risk women, midwives and MCAs provide home care following hospital discharge, for the first week of the postnatal period.

Currently, the resources are not available to provide continuous care to all women during labor in routine midwifery- or obstetric-led care. In fact, continuous care is provided in less than 30% of all cases [12]. At the same time, nationwide, there has been a steep rise in the use of epidural analgesia (EA) amongst primiparous women, from 17% in 2006 to 43% in 2018. In our region, more than half of all women delivering their first baby uses EA. [12] EA is associated with transfer of care, maternal fever, an increased risk of an instrumental delivery, and admittance of the baby due to antibiotic treatment [13]. These outcomes also result in a considerable rise in costs. We hypothesize that adding MCAs to standard maternity care for the provision of continuous support during delivery will be a cost-effective intervention. We predict that any extra costs associated with providing this care will be outweighed by the savings associated with the reduction in EA use. Finally, we predict that the intervention will not decrease patient satisfaction or lead to an increase in complications.

## Methods

### Study design

This Continuous of Care Trial (CCT) will be a two-armed, multi-center randomized controlled trial in midwifery-led and obstetric-led care facilities in the southeastern region of the Netherlands. It will compare the effects of continuous care (CC) provided by a trained maternity care assistant during labor (intervention group, CC group) to care-as-usual (control group, CAU group). We define continuous care as care that is given during the entire first stage of labor by a trained maternity care assistant (MCA), who can offer emotional, informational, physical and practical support. While having no direct medical responsibilities (due to level of training and experience) the MCA is trained in signaling Obstetric emergencies and therefore able to contact the responsible care provider when necessary. MCAs will be asked to be present at the birth from the moment the responsible maternity care provider states that labor has started.

### Study setting and population

All primiparous and multiparous women planning to have a vaginal birth in the southeastern region of The Netherlands will be eligible to participate in this study, including women planning a home or hospital birth in midwifery-led and obstetric-led care. Exclusion criteria will include being under the age of 18, being unable to speak, read or write the Dutch language, and women with a planned cesarean delivery.

### Study outcomes

Our main outcome measure will be the use of epidural analgesia (EA). Secondary outcomes will be (1) referrals from primary care to secondary care, (2) caesarean delivery, (3) instrumental delivery, (4) adverse outcomes associated with epidural (fever, augmentation of labor, prolonged labor, postpartum hemorrhage, duration of postpartum stay in hospital for mother and/or newborn), (5) cost-effectiveness, (6) budget impact analysis and (7) women’s satisfaction with the birth experience.

### Sample size calculation

We calculated that, in order to be able to detect a reduction in use of EA from 25 to 17% (with an alpha 0.05 and beta 0.20), taking into account the use of multilevel analysis (10% higher sample size) and an attrition of 10% (90% complete records), a sample size of 2 × 496 participants will be necessary (*n* = 992).

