### Randomization

Once informed consent has been given, the participant will be asked to fill out some baseline questionnaires. Subsequently, participants will be randomly assigned (using sealed, blank envelopes) to either the intervention or the care-as-usual group. A list based on block randomization with a random block size, using https://www.randomizer.org, will be used for the order in which to fill the envelopes. Randomization will be stratified for different maternity care agencies to prevent the occurrence of any potentially confounding variables based on the location of the two agencies. Stratification will also be done for parity; this is an important determinant of use of EA with a two to three-fold higher uptake in primiparous women compared to multiparous women [12, 14].

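### The unsourced 25% control rate for epidural use is hard to reconcile with the article's own regional and parity figures, so the 80% power for an 8-point reduction is not secure

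*Protocol article*

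**What the plan says.** The Sample size calculation section of the protocol article plans to "detect a reduction in use of EA from 25 to 17% (with an alpha 0.05 and beta 0.20". It raises the result by a tenth because the analysis will be multilevel, then allows for one record in ten being incomplete, and arrives at 496 women per arm, 992 in all. The Methods part of the Abstract repeats these figures. Neither place gives a source for the 25% or says whether the test is two-sided.

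Three other statements bear on the 25%:

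- Background, regional rate: "In our region, more than half of all women delivering their first baby uses EA".
- Background, national rate: use rose "amongst primiparous women, from 17% in 2006 to 43% in 2018".
- Randomization, on parity as a stratification factor, with multiparous women as the comparator: "this is an important determinant of use of EA with a two to three-fold higher uptake in primiparous women".

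The Study setting and population section admits both parities from the same region and excludes planned caesareans. It sets no parity quota and gives no expected share of primiparous women.

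**The concern.** The overall control rate is a weighted average of the primiparous and multiparous rates. If primiparous women are above 50% and multiparous women are at a half to a third of that, multiparous use alone is at least about 17–25%. An overall 25% then sits at or near the multiparous rate and leaves little room for first-time mothers in the trial.

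This matters because the variance of a proportion grows as the rate moves from 25% towards 50%. If the true control rate is higher and the effect stays at 8 percentage points, 992 women give less than 80% power for the primary outcome. At 25%, a reduction of 8 points and a reduction of 32% in relative terms (17/25 = 0.68) are the same thing. At a higher control rate they separate, and the article does not say which one the trial is meant to detect.

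**Working it through.** **1. The plan's own figure.** Inputs from the Sample size calculation section: 25% against 17%, alpha 0.05 (two-sided assumed), power 0.80. Pooled two-proportion formula, with p̄ = 0.21:

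n = [1.96 √(2 p̄(1 − p̄)) + 0.842 √(0.25·0.75 + 0.17·0.83)]² / 0.08² = 405.7, so 406 per arm.

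406 × 1.10 / 0.90 = 496.2, which matches the stated 496. A one-sided test would give 391 and a continuity correction 527, so a two-sided uncorrected test was evidently used.

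**2. What an overall 25% requires.** Let P be the primiparous rate, r the ratio of primiparous to multiparous uptake and f the primiparous share. The overall rate is f·P + (1 − f)·P/r, so the share needed for 25% is f = (0.25 − P/r) / (P − P/r). With P = 0.50, the lower bound of the regional statement:

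| r | multiparous rate P/r | f needed for 25% |
|---|---|---|
| 2 | 25.0% | 0% |
| 2.5 | 20.0% | 16.7% |
| 3 | 16.7% | 25.0% |

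A value of P above 0.50 lowers these shares further. At P = 0.55 and r = 3, for example, f is 18.2%.

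**3. Control rate at an assumed parity mix.** The article does not give f. I assume 40–55%, with P = 0.50:

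- r = 3: 0.40·0.50 + 0.60·0.167 = 30.0%, up to 0.55·0.50 + 0.45·0.167 = 35.0%.
- r = 2: 0.40·0.50 + 0.60·0.25 = 35.0%, up to 0.55·0.50 + 0.45·0.25 = 38.8%.

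**4. Power for the fixed sample.** If both allowances are used up, the effective size is 496 × 0.9 / 1.1 = 405.8 per arm. Using the same pooled two-sided test:

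| Control rate | Power, 8 points absolute | Difference detectable at 80% power | Power, risk ratio 0.68 |
|---|---|---|---|
| 25% (plan) | 80% | 8.0 points | 80% |
| 30% | 73.9% | 8.6 points | 88% |
| 35% | 69.4% | 9.0 points | 94% |
| 37.5% | 67.6% | 9.2 points | 96% |
| 38.8% | 66.8% | 9.3 points | 97% |

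**5. Sensitivity.**

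- *National rate.* With P = 0.43, the same shares give 25.8% (f = 40%, r = 3) to 33.3% (f = 55%, r = 2), and power for 8 points of about 79% down to 71%. An overall 25% is reached at f = 37% with r = 3.
- *Allowances unused.* With all 496 per arm and no design effect, power for 8 points is about 82% at a 30% control rate and 75% at 38.8%.
- *Higher regional rate.* With P = 0.55, r = 2 and f = 55%, the control rate is about 43% and power for 8 points about 65%.

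**The case against.** A reader might infer that the article contradicts itself and that its figures imply a control rate of 30–39%. The documents do not support that reading, for four reasons:

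- The 30–39% range needs a primiparous share that appears nowhere in the article. A 25% rate remains possible with few primiparous women and a three-fold ratio.
- The figures may not share a base. The rate above one half is regional, but the two- to three-fold ratio is not said to be. With the national 43%, a three-fold ratio and a 40% primiparous share, the overall rate is 25.8%, almost the planned value.
- Trial participants are consenting women recruited through two maternity care agencies, including some who plan a home birth. Their EA use need not equal the regional rate.
- The direction of the power error depends on the scale of the effect. With the relative reduction held constant, the trial has more power than planned.

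There is also a point about consequence. The article's cost argument sets about 225 euros per woman against about 2200 euros per EA. Read as an absolute difference, that breaks even at 225/2200 = 10.2 points. For a difference of that size, power would still be about 92% at a 30% control rate and 87% at 38.8%.

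All of this stands as a limit on the claim, but it does not remove the difficulty. The national reading replaces the regional rate that the article itself reports and takes the most favourable end of the ratio. The selection argument is reasonable, but its size is unknown and the article does not use it to justify 25%. The cost benchmark concerns a larger effect than the one the trial is powered for. Nor can the gap be put down to condensation: the 25% is a stated design input that fits poorly with other stated figures.

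**Conclusion.** The concern holds in a conditional form. The 25% is unsourced and hard to reconcile with the regional primiparous rate and the parity ratio, unless at most a quarter of participants are primiparous. It is a questionable input, not an arithmetic error and not a strict contradiction.

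The fall in power for 8 points, from 80% to about 67–74%, rests on four assumptions: a primiparous share of 40–55%, a regional primiparous rate of 50% that carries over to participants, an effect that stays at 8 absolute points, and full use of both 10% allowances. Changing the second to the national rate gives about 71–79%. Changing the third to a constant risk ratio reverses the direction, to about 88–97%. It would therefore be wrong to conclude that the trial is underpowered without qualification. What the article does not secure is its claim of 80% power for the absolute difference it names.

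**What to change.** In the Sample size calculation section, and in the Abstract where the figures recur:

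1. Derive the control rate from regional parity-specific EA rates, weighted by the expected parity mix of participants, and give the source. If 25% is kept because participants are expected to differ from the region, say so and give the reason.
2. State whether the target is an absolute reduction of 8 points or a relative reduction of 32%.
3. For the fixed n = 992, restate the power or the difference detectable with 80% power at the derived rate, over a range of parity mixes. The 67–74% and 8.6–9.3 points shown here illustrate the calculation and should be replaced by values from the authors' own parity mix.

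The cost is a rewritten paragraph. No extra enrolment is needed. The downside is that the stated power will probably look less favourable if the 8-point absolute target is kept.

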### Recruitment

The intervention will be provided by the two largest maternity care agencies in the southeastern region of Limburg. The recruitment will be carried out by intake-staff of the maternity care agencies, who have been trained by the principal investigator. Each pregnant woman registering for postnatal care at one of these agencies (usually in the first trimester of pregnancy) will be informed about the study by telephone or e-mail and will then receive further information by telephone or e-mail. At the standard home visit around 34 weeks of gestation, the intake-staff will answer any remaining questions about the study. If the woman is willing to participate, an informed consent form will be signed. To optimize recruitment, all midwifery practices and the participating hospitals will be informed about the study and asked to inform the women in their care about the study.

### Randomization

Once informed consent has been given, the participant will be asked to fill out some baseline questionnaires. Subsequently, participants will be randomly assigned (using sealed, blank envelopes) to either the intervention or the care-as-usual group. A list based on block randomization with a random block size, using https://www.randomizer.org, will be used for the order in which to fill the envelopes. Randomization will be stratified for different maternity care agencies to prevent the occurrence of any potentially confounding variables based on the location of the two agencies. Stratification will also be done for parity; this is an important determinant of use of EA with a two to three-fold higher uptake in primiparous women compared to multiparous women [12, 14].

### Intervention

If a woman has been randomly assigned to continuous care, she (or her partner) will call the MCA for support at the onset of labor. Since this can be a subjective interpretation, we define the onset of labor as the moment the midwife or doctor confirms that labor has started. In the case of induction of labor, we decided that the MCA will be called for continuous support at the point in time when the membranes are artificially ruptured. On average, the MCA needs approximately 45 min to get to the destination. The MCA will provide care that is tailored to the needs of the woman in labor, such as helping with relaxation, offering massage or breathing exercises, or being present and giving verbal reinforcement. The duration of CC is defined as the moment the MCA arrives until the start of active pushing in the second stage of labor.

### Data collection

Data will be collected at three moments in time (Table 1). Baseline demographic and obstetric characteristics will be collected before randomization. At this point, the questionnaire also includes:
The EQ5D, a standardized validated instrument measuring five health dimensions (mobility, self-care, daily activities, pain and discomfort, and anxiety and depression) that allows us to asses health in individuals or populations [15, 16];The Cambridge Worry Scale (CWS), a validated instrument used to measure the extent and content of worries in specific situations (socio-medical, own health, socio-economic and relational) [17];The State-Trait Anxiety Inventory (STAI) questionnaire, a validated instrument that measures two types of anxiety: state and trait [18, 19].

**Table 1 Tab1:**
[figure not shown]
Timeline and Data Collection. EQ. 5 D Standardized validated instrument measuring five health dimensions. STAI State-Trait Anxiety Inventory

*Control of in- and exclusion criteria (i.e. reason for removal from study: elective caesarean because of breach position).

*EQ5D* Standardized validated instrument measuring five health dimensions; *STAI* State-Trait Anxiety Inventory; *CWS* Cambridge Worry Scale; *LAS* Labor Agentry Scale; *CLIK-Q* Questionnaire to reflect on patient satisfaction (maternity empowerment/experience)

In the first week after birth (preferably the same day of the birth), the MCA will fill-out a case report form together with the midwife or doctor, based on primary and secondary outcome measures. Additionally, the woman will fill out the Labor Agentry Scale (LAS) questionnaire, which scores experience of personal control during labor. In field studies, the LAS showed an inverse relationship between anxiety and control [20].

Six weeks after birth, the participants will fill out the final questionnaire, the CLiK questionnaire, used within Dutch maternity care agencies to reflect on patient satisfaction. It is based on the validated Maternity Empowerment Questionnaire. Questions are about maternity empowerment, the EQ5D and women’s experiences with maternity care assistance. We will perform random checks of the completed case reports and we will extract data from the main source if there are inconsistencies in completed case report forms.

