### Statistical analysis

Baseline characteristics include age in years, ethnic background, gravidity and parity, gestational age at birth, mode of birth in this pregnancy, and if applicable, mode of previous birth and experience of previous birth(s). The primary outcome EA, and its association with continuous care versus care-as-usual, will be analyzed using multilevel logistic regression analysis.

The secondary outcomes are listed in Table 2, and will be addressed using multilevel linear regression analyses (for continuous variables), multilevel logistic regression (for binary variable variables) or multilevel multinomial logistic regression analysis (for categorical outcomes with more than two categories). If important baseline characteristics will differ greatly between the study arms, we will include them in the analysis. Missing data will be imputed by use of stochastic regression imputation, with predictive mean matching as the imputation model. We will perform both an intention to treat analysis and per protocol analysis. Cost-effectiveness will be calculated for the six-week period following childbirth and incremental cost effectiveness ratios will be calculated in QALY per prevented EA based on utility index from the EQ5D and usage of healthcare. Standardized sensitivity analysis will be carried out to quantify the outcome. A budget impact analysis will be performed using ISPOR guidelines, which take into account the financial consequences of the implementation of maternity care assistants as providers of continuous support during labor.

**Table 2 Tab2:** Secondary Outcome Measures

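### The clinical form is due in the first week, preferably on the day of birth, too early for stay durations and later events; no health-care-use collection is visible for the rest of the six-week cost window

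*Protocol article*

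**What the plan says.** The Data collection section fixes the number of contacts: "Data will be collected at three moments in time (Table 1"). They are before randomization, the first week after birth, and six weeks after birth.

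The clinical form belongs to the second contact. The text after Table 1 says: "In the first week after birth (preferably the same day of the birth), the MCA will fill-out a case report form", and continues: "together with the midwife or doctor, based on primary and secondary outcome measures". Random checks of completed forms are planned, with recourse to the source record where a form is inconsistent.

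The outcomes concerned include, in Study outcomes, "duration of postpartum stay in hospital for mother and/or newborn". Table 2 adds durations of home care, hospital care, NICU and intensive care. It also lists antibiotic use, proven infection, blood transfusion, neonatal admission and neonatal death.

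The third contact is described as follows: "Six weeks after birth, the participants will fill out the final questionnaire, the CLiK questionnaire". On its content: "Questions are about maternity empowerment, the EQ5D" and experience with maternity care assistance.

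The Statistical analysis section sets the economic horizon: "Cost-effectiveness will be calculated for the six-week period following childbirth". Its inputs are the EQ5D utility and health-care use.

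**The concern.** A duration can be recorded only when it has ended, and an event only when it has happened. The plan asks for both on a form whose preferred completion date is the day of birth and whose latest date is the end of the first week. If a newborn is still admitted when the form is closed, the recorded stay is too short. An infection or death after closure is recorded as absent.

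The error would be hard to see afterwards. A form closed during an ongoing stay is internally consistent, so the stated check would not send anyone to the source record. The field is filled, so the planned imputation would not touch it. If the field were left blank instead, the imputed values would come from finished stays, which are the shorter ones.

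At stake are the duration and later-complication outcomes and, through health-care use, the cost-effectiveness and budget impact analyses. The Background names admission of the baby for antibiotic treatment among the consequences of epidural analgesia. Of the consequences it names, that admission and its length are the most exposed to early closure.

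**Working it through.** The plan gives no figure for this point that could be reproduced. Its sample size rests on epidural use alone and is not touched.

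**Step 1: when each outcome is known, against when the form closes.**

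| Outcome | Known by | Same-day form | Day-7 form |
|---|---|---|---|
| Epidural use, mode of delivery, fever during labor | Birth | Captured | Captured |
| Ordinary short hospital stay | Discharge | Truncated if the stay continues | Mostly captured |
| Home care | End of the care period | Not captured | Largely captured |
| Long hospital, NICU or intensive-care stay | Discharge | Truncated | Truncated if past day 7 |
| Proven infection, antibiotics, neonatal death | Any later day | Early events only | Events to day 7 only |

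The home-care row follows from the Background: "midwives and MCAs provide home care following hospital discharge, for the first week of the postnatal period".

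**Step 2: share of the cost window after the form.** Inputs: a window of 6 × 7 = 42 days (Statistical analysis) and form completion on day d, from 0 to 7 (Data collection). Share after the form = (42 − d)/42.

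- d = 0, the preferred day: 42/42 = 100%
- d = 1: 41/42 = 98%
- d = 7, the latest day: 35/42 = 83%

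So the form covers at most 7/42 = 17% of the window. This counts days, not euros. Labor care, the epidural and much of the first-week home care fall early, so the share of cost missed is smaller than the share of days and cannot be computed from the article.

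**Step 3: size of the truncation.** A stay of length L on a form closed at day d is recorded as min(L, d). The documents give no stay lengths. As an illustration only, assume exponentially distributed stays with a mean of 7 days for an admitted newborn, counted from birth. The mean recorded stay is then 7(1 − e^(−d/7)).

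- d = 1: 7(1 − e^(−1/7)) = 0.93 days, so 87% is lost
- d = 7: 7(1 − e^(−1)) = 4.42 days, so 37% is lost

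The fraction lost is e^(−d/mean): smaller for shorter mean stays, larger for longer ones. With no admission rate in the article, this cannot be turned into an effect per randomized woman.

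**Step 4: does the six-week contact fill the gap?** Its listed content is empowerment, EQ5D and experience with maternity care assistance. The instruments abbreviated under Table 1 are EQ5D, STAI, CWS, LAS and CLIK-Q; none is a resource-use instrument. The visible text therefore supplies utilities at six weeks but no health-care use after the form.

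**The case against.** **The source may be stated elsewhere.** Table 1, the document's own schedule, is not shown, and an article may leave the source of resource-use data to the full protocol or an economic plan. This stands. The cost part of the point can therefore only ask that the collection be stated or added. It does not remove the first part, because the form's timing and content are stated and conflict with the listed outcomes.

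**Same-day completion is only a preference.** By day 7 most ordinary stays and much of the home care could be recorded. This also stands, and limits certain truncation to same-day forms. But it is the earlier date that the plan prefers.

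**Three stronger readings are tempting and are not supported.**

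- A reader might infer that the harms attributed to epidural analgesia are lost in general. Instrumental delivery and fever during labor are known at birth.
- A reader might infer bias in favor of continuous care, since an MCA attends those labors and could complete the form the same day. But the Background also has MCAs assisting midwives late in labor under usual care, and home care after discharge goes to low- and high-risk women alike. One timing rule is written for both arms. Earlier closure under continuous care is possible, mainly relative to obstetric-led usual-care births, but nothing shows it.
- A reader might set a small recording difference against the plan's cost margin: 225 − 0.08 × 2200 = 49 euros per woman at the design effect. At an assumed 400 to 800 euros per hospital day, 49/800 = 0.06 to 49/400 = 0.12 day would equal it. Those day prices are not in the documents, and the 2200 euros already allows for complications, so adding hospital days risks double counting.

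**Conclusion.** The point holds for the secondary outcomes and the economic analysis. As written, the form's timing does not fit the stay durations and later events it has to carry. Loss is certain for anything still running or yet to occur when a same-day form is closed, and partial for a day-7 form. Neither the inconsistency check nor the imputation would recover it.

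At least 83% of the days in the cost window lie after the form, and the visible text names no health-care-use collection for them. That second statement is limited to what can be read here.

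The primary outcome is unaffected. How much the duration or cost comparison would change, and in which direction, cannot be established from the article. This should be fixed, but it does not threaten the main result.

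**What to change.** 1. Keep the early form for labor and birth items: epidural use, mode of delivery, blood loss, Apgar score and fever during labor.
2. For duration, admission, infection, antibiotic, transfusion and death items, drop the same-day preference. Close them at discharge of both mother and newborn, under the same rule in both arms.
3. Collect health-care use, and later infection or death, up to six weeks. Use a few added questions in the existing six-week questionnaire or extraction from records. If this is already planned, state the source and its timing.
4. Record the form's completion date, so that timing can be compared between arms.

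The cost is a form revision, slightly more questionnaire burden, and later closure for women or newborns with long stays. No new contact and no change in sample size is needed.
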